### Implications of COVID-19 on study delivery

This study is being rolled out during the COVID-19 global pandemic. Therefore, current public health restrictions in place relating to COVID-19 will be followed, aiming to reduce in-person contact with participants to reduce the risk of transmission for patients and staff, where possible (Table 2). Recruitment to the study was open both pre- and post-suspension due to COVID-19; as such, participants recruited to the trial pre-suspension were cluster-randomised in a 1:1 ratio and received an in-person intervention, while participants recruited post-suspension are individually randomised in a 2:1 ratio and receive remote delivery of the intervention as outlined in Table 2.

**Table 2 Tab2:** Proposed protocol changes in response to COVID-19

Study activity	Measures taken
Recruitment	Study information will be shared via email, where possible, or post. Screening visit will be completed via telephone. Consent form will be completed and returned by post or email, where possible. Participants can identify a carer to support them. Carer consent will be obtained. Rolling recruitment will take place as there will be no group component to the intervention and to reduce clinician burden when delivering the intervention.
Randomisation	Participants will be randomised at individual level (due to practicalities of rolling recruitment, e.g. to ensure allocation concealment as participants from the same residential setting may enrol at different times) to either intervention or control group in a 2:1 ratio after completion of the baseline assessment. The allocation ratio was changed to ensure sufficient number of participants are exposed to the intervention and optimal information on intervention delivery can be collected, given that there may be recruitment challenges with remote recruitment and delivery. With 2:1 allocation ratio, two-thirds of participants enrolled will be randomised to the intervention group. Allocations will be undertaken using a permuted block design with unequal block sizes (of 3, 6, 9). A researcher independent of the study will generate the randomisation sequence and allocate the participant after baseline data collection. The randomisation sequence will be concealed from members of the research team involved in participant management to prevent biased allocation [47, 48].
Intervention delivery	Education session (both intervention and control groups) will be delivered remotely via telephone or video conference depending on technology accessible to the individual. Study materials will be posted to participants. Instructions will be sent via email or post and the researcher will provide additional instruction via telephone or video call. Fortnightly coaching calls will be delivered remotely by telephone or video call. Delivery of the weekly group walk will depend on current guidance regarding physical distancing.
Outcome assessment	Participants will be given the option to complete questionnaires via email, post, telephone or video call. This will include using alternative versions of tools that are suitable for remote delivery, where required i.e. using the Blind-MoCA, which omits requirement of pencil and paper or visual stimulus, and is suitable for telephone administration of the test [49]. Accelerometers will be posted to participants with instructions and the researcher will provide additional instruction via telephone or video call. Anthropometric measures will be collected from patient files, where available. Exploration of remote methods of collecting data related to functional mobility, i.e. replacing the Timed-Up-and-Go test with a remote Sit-to-Stand test [50]. Interviews with participants, clinicians and carers will be carried out by telephone or video call.

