### Recruitment

Recruitment to the trial will be via mental health teams in NI and ROI and will involve a number of strategies. The research team will work closely with the multidisciplinary mental health team clinicians and the Northern Ireland Clinical Research Network Mental Health group, where available, to identify service users who meet the eligibility criteria. Recruitment will be via screening clinic lists, referral from existing services, such as groups, day-care services and residential facilities, and through posters displayed in communal and waiting areas. Service users who meet the eligibility criteria will be given information about the study, either at a clinic visit or via post. Those who express an interest in taking part will be invited to meet with the researcher to complete the GPPAQ and PAR-Q and be given the opportunity to ask any questions they have about the study. Following this, if interested in participating in the study they will be asked to provide written consent.

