### Control

Participants assigned to the control group will be invited to attend a single one-to-one information session where they will be given an A5 leaflet briefly outlining the benefits of being more active and reducing sedentary behaviour and advice on how to do so. During the session, the researcher will read through the leaflet with the participant and give them the opportunity to ask questions. The researcher will complete a pro-forma with details of the duration of the session and a checklist of information to be covered in the session. At the end of the session, they will be informed of the date of end of study assessment. Immediately after the session, the researcher will make a handwritten note of the conversation and comments.

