## Trial status

This trial is ongoing and open to recruitment.

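### Table 2 publishes the block sizes (3, 6, 9) while the individually randomised phase is still recruiting, which modestly weakens allocation concealment

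*Protocol article*

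**What the plan says.** Under the COVID-19 changes, "participants recruited post-suspension are individually randomised in a 2:1 ratio" and entered on a rolling basis (protocol article, Implications of COVID-19 on study delivery). The Randomisation row of Table 2 gives the block design: "Allocations will be undertaken using a permuted block design with unequal block sizes (of 3, 6, 9". An independent researcher generates the list and allocates each person after baseline. The row adds: "The randomisation sequence will be concealed from members of the research team involved in participant management to prevent biased allocation". The Trial status section says: "This trial is ongoing and open to recruitment".

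On who meets participants, the Recruitment section says "Those who express an interest in taking part will be invited to meet with the researcher to complete the GPPAQ and PAR-Q". The Control section, written for the in-person design, says "During the session, the researcher will read through the leaflet with the participant and give them the opportunity to ask questions". For the remote phase, Table 2 says "Instructions will be sent via email or post and the researcher will provide additional instruction via telephone or video call", without naming an arm. The article does not say whether the block order is random, how often each size is used, whether the list is stratified by service, or whether anyone is masked.

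**The concern.** Concealing a list protects it only if the next entry cannot be inferred from earlier ones. Here the smallest block holds two intervention places and one control, all three sizes are in print, and people enter singly. Allocation shows itself in practice: one arm gets fortnightly coaching and an activity monitor, the other a single session. Clinicians and the researcher identify, approach and baseline service users, so they have some influence on timing.

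If staff can foresee the likely arm, a keen or a reluctant service user could be brought forward or held back, even without intent. The effect estimates are unadjusted mean changes, so an imbalance in motivation would pass straight into the estimate used for the efficacy criterion in Table 1. Analysis cannot reliably remove selection on unmeasured motivation.

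**Working it through.** **Inputs from the article.** Individual 2:1 allocation; block sizes 3, 6 and 9; rolling entry; total target 60 over both phases. The number in the remote phase is not given, so 20 to 60 is used as a range.

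**Assumptions.** One unstratified list; sizes equally likely and in random order; an observer who sees every past allocation and updates by Bayes' rule.

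**The plan's own figure.** Blocks of 3, 6 and 9 hold 2+1, 4+2 and 6+3 places. Each is exactly 2:1, so the statement "With 2:1 allocation ratio, two-thirds of participants enrolled will be randomised to the intervention group" is reproduced. Always guessing intervention is right 66.7% of the time, which is the benchmark.

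**Hand checks at the start of the list.**
- After one control: the first place is a control with probability 1/3 for every size, so the sizes stay equally likely. P(next is control) = (0/2 + 1/5 + 2/8)/3 = 0.15.
- After two interventions: the likelihoods are 2/3 × 1/2 = 0.333, 4/6 × 3/5 = 0.400 and 6/9 × 5/8 = 0.417 for sizes 3, 6 and 9. P(next is control) = (0.333 × 1 + 0.400 × 2/4 + 0.417 × 3/7)/(0.333 + 0.400 + 0.417) = 0.712/1.150 = 0.62.
- After three controls: with these sizes the block can only be 9, so the next six are certain to be intervention. An observer who allows for 12 or 15 cannot conclude this.

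**Simulation, sizes known (20,000 sequences per setting).**

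| Remote participants | Next allocation certain | Correct guesses | Sequences with at least one certain prediction |
|---|---|---|---|
| 20 | 3.3% | 72.9% | 22% |
| 30 | 3.5% | 73.5% | 33% |
| 60 | 3.7% | 73.7% | 58% |

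The next allocation is at least 90% sure for 13–14% of places. At 30 to 60 participants, about 13% of places are near-certain intervention and only 0.7% near-certain control.

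**What the disclosure itself adds.** The right comparison is with blocks whose sizes the observer does not know, represented by an observer who allows 3, 6, 9, 12 or 15. The last column assumes that staff place keen people in the third of places least likely to be control and less keen people in the third most likely, with half of all participants keen.

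| Scenario (30 to 60 participants) | Certain | At least 90% sure | Correct guesses | Keen share, WORtH vs control |
|---|---|---|---|---|
| 3/6/9, sizes known | 3.5–3.7% | 13–14% | 73.5–73.7% | 62% vs 26% |
| 3/6/9, sizes unknown | 0% | 0.7% | 73.4–73.6% | 62% vs 26% |
| 6/9/12, sizes unknown | 0% | 2.6–2.8% | 71.3–71.5% | 60% vs 30% |

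The keen shares in the first row follow from control shares of 0.10, 0.325 and 0.575 by third. WORtH: (0.90 + 0.5 × 0.675)/2.0 = 0.62. Control: (0.10 + 0.5 × 0.325)/1.0 = 0.26.

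**Sensitivity.** If small blocks dominate (0.6/0.3/0.1), 36% of allocations are at least 90% sure and 1.5% are certain. If the block order were also known, for example a repeating 3-6-9, about 27% would be certain; the article does not disclose an order.

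**The case against.** Most of the predictability is not caused by the disclosure. Withholding the sizes leaves correct guesses at about 74% and the keen split at 62% versus 26%. Both come from blocking with visible allocations, and a new blocked list keeps most of them. This stands, and neither figure should be charged to the printed sizes.

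The real safeguards remain: an independent allocator, a hidden list, allocation after baseline, and varying block sizes. A reader might infer that staff can often predict the next arm, or that the protection is not delivered. Neither is supported: certainty is about 4%, and the gain over always guessing intervention is about 7 percentage points.

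The figures also need one person who sees everything. Recruitment runs through three services, and the article does not show that the researcher named in several places is a single person or who delivers the remote control session. That makes the figures near worst case. Lack of masking is likewise an inference from the contrast between arms, though the only practical reading.

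Finally, a reader might infer that the retention and adherence criteria would be inflated. Retention in Table 1 counts recruited participants without splitting by arm, so moving keen people between arms would not obviously raise it. An effect on adherence is possible but has not been quantified.

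What survives is narrower: printing the sizes creates the certain predictions and most of the near-certain ones, and nothing is gained by printing them during recruitment.

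**Conclusion.** The concern holds as a modest weakness. Disclosing block sizes with a minimum of 3 during open, rolling recruitment works against the concealment stated in the same row. Its own contribution is to raise certain predictions from 0% to about 4%, and those at least 90% sure from about 1–3% to 13–14%. Nearly all are predictions of intervention, which is already the likelier arm. These sizes rest on a single list, full sight of past allocations, and equally likely sizes in random order. Where staff see only their own service's participants, predictability is lower. The documents give no evidence that any allocation has been anticipated or that the arms are biased. The case for acting is that the remedy is cheap and recruitment is still open.

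**What to change.** For participants not yet randomised, the independent researcher should discard the remainder of the current list and generate a new 2:1 sequence. Its block sizes should be undisclosed and in random order, preferably without blocks of 3. They should be held in a restricted document unavailable to anyone who screens, enrols or treats participants. Table 2 should read: *permuted blocks of varying size; sizes withheld until recruitment closes*. The results should report how many participants were allocated under the disclosed sizes.

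The cost is about an hour for the independent researcher and one changed sentence, with no extra participants or visits. The downside is a possible one-off departure from exact 2:1 where the old list is cut mid-block. The worst case is a block of 9 cut after six interventions (6 against 6 × 2/3 = 4 expected) or after three controls (3 against 1 expected), a shift of two participants. The new list removes the certain predictions and most near-certain ones; it does not remove the predictability inherent in blocking.

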## Discussion

This randomised controlled feasibility study will evaluate the feasibility and acceptability of a multi-component behaviour change intervention to increase physical activity and reduce sedentary behaviour of adults with SMI living in rural and semi-rural environments.

Additionally, this study will address the challenges and implications of remote delivery of the WORtH intervention due to the COVID-19 pandemic. There is limited evidence on the feasibility and acceptability of remotely delivered interventions for the management of SMI [51, 52], and we are not aware of any remotely delivered interventions aimed at improving physical activity and sedentary behaviour in this population. The findings will inform the design of a future definitive randomised controlled trial if it is shown to be feasible.

## Trial status

This trial is ongoing and open to recruitment.

## Data Availability

Data and materials can be requested from the corresponding author.

## Abbreviations

BCTTv1: Behaviour Change Techniques Taxonomy version 1
BREQ-2: Behavioural Regulation in Exercise Questionnaire version 2
GPPAQ: General Practice Physical Activity Questionnaire
MoCA: Montreal Cognitive Assessment
NI: Northern Ireland
PAR-Q: Physical Activity Readiness Questionnaire
PNSE: Psychological Need Satisfaction in Exercise Scale
RoI: Republic of Ireland
SBQ: Sedentary Behaviour Questionnaire
SIMPAQ: Simple Physical Activity Questionnaire
SMI: severe mental health difficulties
TUG: Timed Up-and-Go
WEMWBS: Warwick-Edinburgh Mental Wellbeing Scale
WORtH: Walking fOR Health
